### **5.6.5.3      Complement activation**

Determination of complement activation (usage) by measuring the pool for complement factor C3 will be performed at selected visits; refer to Tables 6 - 14 in Appendix 2 for the exact time points. The samples will be collected and processed according to standard hospital procedures and assessed by the local laboratory of the participating sites.

### **5.6.5.4      Troponin**

The requirement for measuring troponin was removed with the implementation of this protocol amendment (Amendment 6).

### **5.6.5.5      Inflammatory response**

Determination of inflammatory response by measuring C-reactive protein (CRP), fibrinogen, haptoglobin, MCP-1 and the albumin/globulin ratio will be performed at selected visits; refer to Tables 6 - 14 in Appendix 2 for the exact time points. The samples will be collected and processed according to standard hospital procedures and assessed by either the local laboratory of the participating sites or by the central laboratory (MCP-1).

Monitoring and stopping criteria for inflammation;

CRP >2 x ULN and 2 x reference value taken at Visit 29 (first time CRP was measured in Extension phase of PRO051-02), (along with symptoms/signs of inflammation in the absence of any other likely causative factors)

If criterion is met, test should be repeated immediately. If the result still meets the criterion, the study drug should be discontinued until further investigations are performed to establish the cause.

**OR**

- MCP-1 >2 x reference value taken at Visit 85 (first time MCP-1 was measured in Extension phase of PRO051-02) and Complement C3 < LLN (along with symptoms/signs of inflammation in the absence of any other likely causative factors.)

If criteria are met, tests should be repeated immediately. If the results still meet the criteria, the study drug should be discontinued until further investigations are performed to establish the cause.

**OR**

- CRP, MCP-1, or total C3 are persistently (i.e., on more than 2 consecutive assessments) beyond the threshold levels described above in the absence of inflammation signs/symptoms, or are associated with elevations in fibrinogen or haptoglobin > 2 x ULN

If the investigator believes and/or investigations show other likely causative factors (e.g., acute influenza, acute trauma) are responsible; and/or abnormal laboratory results along with signs/symptoms of inflammation have resolved, these must be discussed with and agreed by the Medical Monitor prior to re-starting study drug. In situations where no alternative cause is established and abnormal laboratory results with the presence of inflammatory signs and symptoms persist, study drug should be permanently discontinued.

### **5.6.5.6      Dystrophin antibodies in blood**

Formation of antibodies to dystrophin in blood will be determined at selected visits, refer to Tables 6 - 14 in Appendix 2 for the exact time points. The collection, processing and shipping of these blood samples to the Prosensa laboratory will be described in the study specific laboratory manual.

For analytical methods refer to Appendix 4.

### **5.6.5.7      Coagulation**

A blood sample for determining the aPTT will be collected at selected visits, refer to Tables 6 - 14 in Appendix 2 for the exact time points. The samples will be collected and processed

according to standard hospital procedures and assessed by the local laboratory of the participating sites. Any subject reaching a threshold value of aPTT of  $\geq 1.5 \times$  ULN should be immediately withdrawn.

#### **5.6.5.8      Cystatin C**

A blood sample for determining cystatin C will be collected at selected visits, refer to Tables 6 - 14 in Appendix 2 for the exact time points. The samples will be collected and processed according to standard hospital procedures and assessed by the local laboratory of the participating sites. In case the assessment is not available at the local laboratory of a participating site, the samples will be analyzed at an external laboratory. The collection, processing and shipping of these blood samples to the external laboratory will be described in the study specific laboratory manual.

#### **5.6.5.9      Urinalysis**

A first morning urine specimen is collected at selected visits (refer to Tables 6 - 14 in Appendix 2 for the exact time points) in order to assess the urinalysis parameters as described in Appendix 3.

At visit 13, 25, 37, 49, 61 and 4 weekly thereafter an additional first morning sample of urine is collected for alpha-1-microglobulin, KIM-1 and cystatin C assessment.

- If during treatment any of the following occur, study drug must be stopped and a 24-hour urinalysis performed as soon as possible but at the latest by the next scheduled visit: urinary protein concentration  $\geq 0.2$  g/L and  $< 0.45$ g/L on two consecutive samples;
  - NOTE: if urinary protein concentration is  $\geq 0.45$ g/L on urinalysis, stop study drug and repeat protein analysis. If the repeat urinary protein value is  $\geq 0.2$ g/L, continue to withhold study drug and perform a 24 hour urinalysis. If the repeat urinary protein is  $< 0.2$ g/L, study drug may be restarted.
- protein/creatinine ratio in the morning sample is  $> 0.5$  on two consecutive samples;
- serum concentration of cystatin C is above the normal range and 50% above the baseline value.

24-hour urinalysis to include creatinine concentrations for creatinine clearance assessment, total protein and protein electrophoresis.

If the results of the 24-hour urinalysis triggered by any of the above do not meet criteria defined in section 5.6.8.2, study drug may be restarted.

The urine samples will be collected and processed according to standard hospital procedures and assessed by the local laboratory of the participating sites.

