#### **5.6.8.2 Renal Toxicity**

Urinalysis (as described in Section 5.6.5.9) will be conducted every 2 weeks during the treatment part of each 12 week cycle. In addition, 24-hour urinalysis will be conducted if any of the criteria described in Section 5.6.5.9 are met on two consecutive weekly samples.

If a subject meets any of the following criteria, study medication will be stopped until such time that the Sponsor (in discussions with the Investigator) considers that the benefit of further treatment with PRO051 outweighs the risk to the individual subject. Given the progressive and fatal nature of this disease, it is important that the renal stopping criteria allow the flexibility for the potential to re-start dosing in this population following an individual subject benefit: risk assessment.

- Proteinuria in 24-hour urine sample is either >300 mg/day or 8 mg/m^2/h (whichever is reached first); or
- Albumin excretion in 24-hour urine sample is >50 mg/day; or
- New appearance of casts (other than hyaline casts up to 200/mL) or erythrocytes (≥5 cells/hpf). An additional fresh spot urine sample will be required for this analysis

Routine non-invasive renal imaging will not be performed for subjects participating in the study. However, if a subject experiences persistent and progressive renal impairment, further investigations which may include non-invasive imaging and renal biopsy will be considered on an individual subject basis.

An aliquot of urine for storage will be collected for potential future analysis for any subject that meets renal stopping and follow-up criteria at any time during the study. Additionally, at Visit 85 (week 68), Visit 117 (week 104) and yearly thereafter or early withdrawal, an aliquot of urine will be obtained and frozen for each subject to allow for storage and potential future analysis of emerging renal biomarkers

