#### **6.4            Discontinuation of study medication**

In case the study medication is stopped for any reason, the Investigator will discuss the reasons with the Sponsor and a decision will be made as to whether the subject is withdrawn from the study or receives further treatment with PRO051 following an individual subject risk: benefit assessment.

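### Section 5.6.5.9: after a raised urinary protein (0.2 to below 0.45 g/L), a second value of 0.45 g/L or more can escape the 24-hour urinalysis that a lower second value makes mandatory

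*Protocol*

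**What the plan says.** Section 5.6.5.9 lists triggers on which "study drug must be stopped and a 24-hour urinalysis performed as soon as possible but at the latest by the next scheduled visit". The protein trigger needs both values to be at least 0.2 and below 0.45 "g/L on two consecutive samples". Two further triggers are a morning protein/creatinine ratio above 0.5 on two consecutive samples, and a serum cystatin C above the normal range and 50% above baseline.

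A note under the protein trigger covers a single value of 0.45 g/L or more: "stop study drug and repeat protein analysis". If the repeat is 0.2 g/L or more, the instruction is to "continue to withhold study drug and perform a 24 hour urinalysis". If it is below 0.2 g/L, dosing may resume. The note does not mention the sample taken before the high one.

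Section 5.6.8.2 adds that "24-hour urinalysis will be conducted if any of the criteria described in Section 5.6.5.9 are met on two consecutive weekly samples". It then gives the renal stopping limits: 24-hour protein above 300 mg/day or 8 mg/m²/h; "Albumin excretion in 24-hour urine sample is >50 mg/day"; or new casts or erythrocytes, for which "An additional fresh spot urine sample will be required for this analysis". Section 6.4 adds a general step: "In case the study medication is stopped for any reason, the Investigator will discuss the reasons with the Sponsor".

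**The concern.** A monitoring rule should not ask for less work-up as the result gets worse. Here it does at one point. Two moderately raised samples commit the investigator to a 24-hour collection, and no later low value lifts that. If the second sample is higher still, the pair no longer meets the capped criterion, and one low repeat is enough to resume dosing.

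The 24-hour collection is what allows the protein and albumin stopping limits of section 5.6.8.2 to be applied. Under section 5.6.5.9 it also supplies creatinine clearance and protein electrophoresis. In the affected sequence a boy with two consecutive raised scheduled samples may be re-dosed without any of these. Section 5.6.5.1 says the drug accumulates in the kidney and is potentially nephrotoxic, and it gives renal monitoring the highest importance.

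**Working it through.** The protocol gives no figure to reproduce here, so the check is to apply the protein rule literally.

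**Inputs**, all from section 5.6.5.9: lower threshold 0.2 g/L; upper threshold 0.45 g/L. Let P be the preceding scheduled sample (below 0.45 g/L), C the current one, and R the repeat that the note requires when C is 0.45 g/L or more.

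**Rule as written.** The 24-hour test is mandatory if

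- 0.2 ≤ P < 0.45 and 0.2 ≤ C < 0.45, or
- C ≥ 0.45 and R ≥ 0.2.

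If C ≥ 0.45 and R < 0.2, the drug may be restarted without it.

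**Rule as proposed.** The 24-hour test is mandatory if

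- P ≥ 0.2 and C ≥ 0.2, or
- C ≥ 0.45 and R ≥ 0.2.

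| P (g/L) | C (g/L) | R (g/L) | As written | As proposed |
|---|---|---|---|---|
| 0.30 | 0.30 | none needed | mandatory | mandatory |
| 0.30 | 0.44 | none needed | mandatory | mandatory |
| 0.30 | 0.45 | 0.19 | **not required** | mandatory |
| 0.30 | 0.50 | 0.10 | **not required** | mandatory |
| 0.20 | 2.0 | 0.19 | **not required** | mandatory |
| 0.30 | 0.45 | 0.20 | mandatory | mandatory |
| 0.10 | 0.50 | 0.19 | not required | not required |

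**Where the reversal lies.** Both versions were run in steps of 0.01 g/L, with C and R from 0.05 to 0.80, to see whether raising C ever removes the mandatory test. As written, every reversal is at the step to C = 0.45, for P from 0.20 to 0.44 (25 values) and R from 0.05 to 0.19 (15 values). That is 25 × 15 = 375 grid cells, which describes the shape of the gap and not how often it occurs. As proposed, there are no reversals. The outcome changes only for P from 0.20 to 0.44, C ≥ 0.45 and R < 0.20, and always towards doing the test.

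**Does the ratio trigger cover it?** The unit of the protein/creatinine ratio is not stated. Assuming g/g, a ratio above 0.5 needs urine creatinine below 0.30 / 0.5 = 0.60 g/L at the first sample and below 0.45 / 0.5 = 0.90 g/L at the second. If both hold, the 24-hour test is forced by that route. If creatinine is at or above either limit on its sample, the ratio trigger does not fire and the gap stays open. The protocol gives no creatinine distribution from which to say how often each case arises.

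**The case against.** The strongest reply is that the two arms do different jobs. The lower arm confirms modest proteinuria with a second scheduled sample and does not stop drug after the first. The upper arm stops drug on one value and asks for an additional test, so in the disputed sequence drug is already off and the newest result is below the protocol's own limit. Asking for a 24-hour collection only when the repeat confirms is a defensible clinical choice. That holds for an isolated spike, and the proposed wording keeps it. It does not explain why a low result is enough after 0.30 then 0.45 g/L when it is not after 0.30 then 0.44 g/L.

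Section 5.6.8.2 could be read as closing the gap, with 0.30 then 0.45 g/L counted as two consecutive samples that each reach a threshold. But it points back to the capped criterion and states no combined rule. It also speaks of weekly samples when the same section schedules urinalysis every 2 weeks during treatment. A reader following 5.6.5.9 would not be sure of it.

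Other safeguards do reduce the weight of the point. The ratio is scheduled with the urine samples in Tables 9 to 14 and will sometimes force the test. Cystatin C is a separate trigger. Restart is permitted, not required, and section 6.4 calls for a discussion and an individual risk-benefit decision. None of these makes the 24-hour test mandatory in this sequence.

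**Conclusion.** The inconsistency is real on the text of section 5.6.5.9, and it is minor. It arises only when the preceding sample is at least 0.2 and below 0.45 g/L, the next is 0.45 g/L or more, and the repeat is below 0.2 g/L, with neither the ratio nor the cystatin C trigger firing. In that case the 24-hour protein and albumin limits need not be checked before re-dosing, although they must be after two lower values. The cast and erythrocyte criterion uses a spot urine and is unaffected.

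There is no dosing through high protein, because drug stops at once at 0.45 g/L. Frequency cannot be derived from the protocol. The conclusion rests on reading 5.6.5.9 literally and on section 5.6.8.2 not being taken as a separate combined rule. No estimate, analysis or dose-escalation decision is affected.

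**What to change.** Make two wording changes in section 5.6.5.9. First, state the protein trigger as 0.2 g/L or more on two consecutive samples, with no upper bound. Second, limit the note's restart on a repeat below 0.2 g/L to a value of 0.45 g/L or more whose preceding sample was below 0.2 g/L.

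The cost is an occasional extra 24-hour urine, a test the protocol already uses, with drug withheld until its result is known. Section 9.6 treats changes affecting subject safety as substantial amendments, so ethics committee and authority approval would be needed. The change could go into the next amendment made for other reasons.

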### **5.6.5.2      Thrombocyte Count**

Thrombocyte count will be performed on a two weekly basis during the treatment part of each 12 week cycle, and the following monitoring and discontinuation criteria apply:

- If thrombocytes are below the lower level of the normal range, thrombocytes will be checked prior to the next scheduled dose of study medication. Study medication will only be administered if thrombocytes are  $>75 \times 10^9/L$ ;
- If thrombocytes are still  $<75 \times 10^9/L$ , they will be checked on alternate days until they reach  $>100 \times 10^9/L$ ;
- If thrombocytes are  $<75 \times 10^9/L$ , study medication will be stopped and will only be considered for re-challenge should a clear alternative (non-drug related) cause be found after discussion between the Sponsor and Investigator;
- If the thrombocyte count has fallen  $>25\%$  from the previous count and is  $<100 \times 10^9/L$  then study medication should not be administered until thrombocytes return to  $>100 \times 10^9/L$ ;
- Investigators should be alert to trends for a consistent decrease in thrombocytes over two or more visits that may not meet the above criteria.

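### After a stop for raised serum cystatin C, the written restart condition tests only urine protein, albumin, casts and erythrocytes, so a boy whose cystatin C has not fallen meets it

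*Protocol*

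**What the plan says.** Section 5.6.5.9 of the Protocol lists three kinds of finding that stop drug and call for a 24-hour urinalysis during the treatment beyond the study period. Two are spot urine measures: urinary protein concentration and the protein/creatinine ratio, each on two consecutive samples. The third is a blood result: "serum concentration of cystatin C is above the normal range and 50% above the baseline value".

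The section then fixes the content of the collection: "24-hour urinalysis to include creatinine concentrations for creatinine clearance assessment, total protein and protein electrophoresis". It closes with one release rule for every trigger. The test is whether the results of the 24-hour urinalysis "triggered by any of the above do not meet criteria defined in section 5.6.8.2, study drug may be restarted".

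Section 5.6.8.2 holds the criteria that this rule points to:

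- 24-hour protein above 300 mg/day or 8 mg/m²/h;
- albumin, worded as "Albumin excretion in 24-hour urine sample is >50 mg/day";
- newly appearing casts (hyaline casts up to 200/mL excepted) or erythrocytes at 5 or more per high-power field.

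The sponsor hold in that section depends on the same list: "If a subject meets any of the following criteria, study medication will be stopped until such time that the Sponsor" judges, with the investigator, that benefit outweighs risk.

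Section 6.4 adds a general rule. After a stop for any reason, investigator and sponsor discuss it, and the boy is either withdrawn or "receives further treatment with PRO051 following an individual subject risk: benefit assessment".

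**The concern.** The stop and the release look at different things. Serum cystatin C is the only one of the three triggers that is not a urine protein measure, yet its stop is released on urine protein, albumin and sediment. Those results can all be clean while the value that caused the stop is unchanged.

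Section 5.6.5.1 gives renal monitoring top priority because the drug accumulates in the kidney and may be nephrotoxic. It also warns that serum and urinary creatinine are hard to read in this disease because muscle mass changes, and it lists serum cystatin C among the renal markers to be used. At stake is renewed dosing of a child with an unresolved renal signal until the next scheduled sample stops the drug again.

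**Working it through.** **Step 1. Set triggers against release criteria.**

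| Stop trigger (5.6.5.9) | Counterpart in 5.6.8.2 |
|---|---|
| Spot urine protein from 0.2 to below 0.45 g/L, two consecutive samples | 24-hour protein; 24-hour albumin |
| Protein/creatinine ratio above 0.5, two consecutive samples | 24-hour protein; 24-hour albumin |
| Serum cystatin C above normal and 50% above baseline | None |

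Creatinine clearance comes from the same 24-hour collection, but 5.6.8.2 sets no threshold for it. Section 5.6.5.8 covers only the sampling of serum cystatin C and adds no restart rule. None of 5.6.5.8, 5.6.5.9 and 5.6.8.2 orders a repeat before restart.

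**Step 2. Test a case.** Suppose cystatin C remains above normal and at 1.5 times baseline, 24-hour protein is at most 300 mg/day and below 8 mg/m²/h, albumin is at most 50 mg/day, and there are no new casts or erythrocytes. No 5.6.8.2 criterion is met. The restart condition is satisfied, and the 5.6.8.2 sponsor hold is not triggered.

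**Step 3. Compare with marker-specific rules.** For a urine protein of 0.45 g/L or more, 5.6.5.9 says "stop study drug and repeat protein analysis", and drug may resume if the repeat is below 0.2 g/L. For a thrombocyte fall of more than 25% to below 100 × 10⁹/L, 5.6.5.2 says "study medication should not be administered until thrombocytes return to" a level above 100 × 10⁹/L. The cystatin C stop has no such link.

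**Step 4. Find the interval to the next scheduled serum cystatin C (Appendix 2).**

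- Table 10, cystatin C row: visits 113, 118, 121, 125, 130, 133. Gaps are 5, 3, 4, 5 and 3 weeks. Tables 11 to 14 repeat the pattern.
- Table 9, cystatin C row: visits 97 and 109. The gap is 109 − 97 = 12 weeks.
- Table 9, safety biochemistry row: visits 89, 93, 97, 101, 106, 109. Gaps are 4, 4, 4, 5 and 3 weeks. This row applies if cystatin C is run with blood biochemistry, where Appendix 3 lists it.

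**Step 5. Count doses before that sample.** Assume restart at the next weekly visit, with the next sample drawn before that day's injection. Dosing visits are 94–101 and 106–109 (Table 9), and 110–113, 118–125 and 130–133 (Table 10). The dose is 6 mg/kg.

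| Stop at visit | Doses before next sample | Number | mg/kg |
|---|---|---|---|
| 113 or 125 (Table 10) | none; 4 weeks off drug | 0 | 0 |
| 118 (Table 10) | 119, 120 | 2 | 2 × 6 = 12 |
| 121 (Table 10) | 122–124 | 3 | 3 × 6 = 18 |
| 161, weekly option (Table 12) | 162–165 | 4 | 4 × 6 = 24 |
| 97 (Table 9), cystatin C row | 98–101, 106–108 | 4 + 3 = 7 | 7 × 6 = 42 |
| 97 (Table 9), biochemistry row | 98–100 | 3 | 3 × 6 = 18 |

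Add one dose if the result is not back before that day's injection. Subtract doses if the 24-hour result takes longer than a week. Under the intermittent regimen, boys above 50 kg are capped at 300 mg per dose, so their totals per kilogram are lower.

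**The case against.** The best reply is section 6.4. It applies after any stop, and for this stop the cystatin C value is itself the reason to be discussed. It brings in the same parties and the same kind of judgement as the 5.6.8.2 hold. Restart is also optional, creatinine clearance will be in hand, and a persistent elevation stops drug again at the next sample. Monthly safety board review and an independent committee that includes a pediatric nephrologist stand behind all this. These are real limits on the harm. But none of them requires a new cystatin C value, so the decision can be taken without one, and the only filtration result available has no threshold and rests on a marker the protocol itself distrusts.

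A second reply is that 5.6.8.2 speaks of criteria met on two consecutive weekly samples before the 24-hour urinalysis, which could imply a second cystatin C. That conflicts with the single-value trigger in 5.6.5.9. It also governs when the urine is collected, not when drug resumes: on that reading, drug could be released after two raised values. It would, however, delay matters and reduce the dose counts.

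A third reply is that many stops here are deliberately released by judgement: the hepatic criteria, the 5.6.8.2 criteria themselves, and thrombocytes below 75 × 10⁹/L, where re-challenge needs a clear non-drug cause. This is fair, and the comparison in step 3 is not a universal pattern. The finding does not depend on it. The fault is a written release condition that does not test the signal behind the stop.

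**Conclusion.** The concern holds. One of the three trigger types has no counterpart among the criteria that release it, and a boy with persistently raised cystatin C and clean urine meets the restart condition as written. The avoidable exposure is limited: 0 to 3 doses under the intermittent regimen of Tables 10 to 14, up to 4 under the weekly option, and 7 or 3 in Table 9 after visit 97, depending on the row used. These counts assume that the 24-hour result and the section 6.4 discussion are complete by the next weekly visit, so they are towards the upper end. The permissive wording and section 6.4 reduce the risk without closing the gap. It is a narrow fault in a paediatric dosing-safety rule, and it should be corrected.

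**What to change.** Amend the restart sentence in 5.6.5.9 along these lines: after a stop for serum cystatin C, drug may be restarted only if a repeat serum cystatin C no longer meets the trigger and no 5.6.8.2 criterion is met. If the repeat still meets the trigger, the 5.6.8.2 sponsor benefit:risk hold applies, and the creatinine clearance already collected is considered in that decision.

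The cost is one sentence by amendment and one unscheduled repeat of an existing blood test, which can be drawn when the 24-hour urine is handed in. A few boys may stay off drug longer before a restart decision. Flexibility is kept, because a persistent elevation leads to an individual decision and not to permanent discontinuation.
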